### 2.8. Data and Statistical Analysis Plan

Basic demographic data and risk factors for meningococcal disease (from the questionnaire), laboratory results and vaccination data will be entered into the study database. IMD and gonorrhoea rates will be obtained from routine surveillance data from the CDC, NT. For the case–control and screening method analyses, data custodians from AIR and CDC NT will link participant records and assign unique study IDs prior to sending data to the study team. No identifying information will be stored in the main study database. Infection rates for IMD and gonorrhoea for various demographic subgroups will be estimated from CDC NT surveillance data, and a many-to-one merge will be used to link background rates to individual records, so as to adjust for these rates in the subsequent analyses.

There are some limitations for observational studies with potential for bias and confounding. Some of the potential sources of bias identified include, any changes to the current practice of notifications over the study period, differences in case ascertainment due to variation in extent of screening and contact tracing, differences in healthcare seeking behaviour for STI treatment and vaccination, extent of other STI prevention/health promotion programs offered in the region, missing data, misclassification of the outcome, differences in lab diagnostics and those lost to follow up during the study period.

To partly mitigate the effects of some of the potential biases, different study designs will be utilized in the investigation of the research hypotheses. This approach will aid in triangulation of findings and strengthen the conclusions that will be drawn from the study [23]. Since there is considerable debate about the circumstances under which causality can be tested or assumed, we will use two different approaches with differing and unrelated key sources of potential biases in assessing vaccine effectiveness. The two are the screening approach and the case–control approach. In the screening approach, results are compared between different populations in different contexts (cross-context comparisons). In the case–control approach, two different control groups will be used, namely controls from the STI notification (Chlamydia) database and the Australian Immunisation register (AIR). These approaches will not give the same estimates of the causal effect unless all analyses are unbiased.

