## 3. Primary Objectives

### 3.1. Evaluation of the Effectiveness of 4CMenB Vaccine against Gonorrhoea in 15 to 19 Year Olds

The primary analysis on vaccine effectiveness (VE) will be performed using a case–control method using controls from the sexually transmitted infections (STI) notification database for chlamydia. A case will be defined as any laboratory confirmed case of gonorrhoea among 15–19-year-olds notified to the CDC. For each case, up to four controls will be randomly sampled from a de-identified dataset of individual records extracted from the Chlamydia notification database of the CDC. Although increasing the number of controls per case increases statistical power, beyond a ratio of four controls per case only small improvements in power are expected [24,25]. A secondary case–control analysis will be performed using controls from the Australian Immunisation register (AIR). For each case, up to 20 controls will be randomly sampled from a de-identified dataset of individual records extracted from the AIR, following restriction of the database to the NT to ensure sampling from the same population. A previous similar study on assessing the effectiveness of the varicella vaccine in Australia has shown maximum precision using 20 controls per case [26]. Controls from both AIR and STI databases will be matched to cases by date of birth ± 4 weeks. Vaccination status of controls will be ascertained from the AIR after selection and vaccination considered valid if received ≥3 months before the date of laboratory confirmation of gonorrhoea in the matched case. This method of control ascertainment has been used previously to assess VE of *Haemophilus influenzae* serotype B, pertussis, varicella and measles vaccines in Australia [26]. Conditional logistic regression models will be generated in Stata to estimate VE.

VE will also be estimated using the screening method for 15–19-year-olds with laboratory-confirmed gonorrhoea within 3 months of receiving two doses of the 4CMenB vaccine. The comparator group will include all 15–19-year-olds in the NT. Using the screening method, VE will be estimated as $1-\frac{PCV(1-PCV)}{PPV(1-PPV)}$ where *PCV* is the proportion of vaccinated MenB cases and *PPV* is the vaccine coverage in the age group being analysed [27]. Vaccine coverage data for each age group will be obtained from the AIR.

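### Section 2.8 reads agreement between the screening and case–control estimates as proof of no bias, but screening and the AIR case–control analysis share cases and reference population and so share their main biases

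*Protocol article*

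**What the plan says.** Section 2.8 of the protocol article offers triangulation as a partial remedy for bias. It says "we will use two different approaches with differing and unrelated key sources of potential biases in assessing vaccine effectiveness", the two being screening and case–control. It describes screening as follows: "In the screening approach, results are compared between different populations in different contexts (cross-context comparisons". Case–control is to use two control groups, chlamydia notifications and the AIR. The paragraph ends: "These approaches will not give the same estimates of the causal effect unless all analyses are unbiased".

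Section 3.1 then specifies the analyses for gonorrhoea.

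- **Primary:** notified laboratory-confirmed cases against chlamydia controls, up to four per case.
- **AIR case–control:** "For each case, up to 20 controls will be randomly sampled", "extracted from the AIR, following restriction of the database to the NT to ensure sampling from the same population". Matching is on date of birth only.
- **Screening:** "The comparator group will include all 15–19-year-olds in the NT", and "Vaccine coverage data for each age group will be obtained from the AIR".

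Section 4.3 applies screening and case–control to invasive meningococcal disease (IMD), with controls from the AIR alone. Section 4.6 carries the alternative VE methods into the cost-effectiveness ratios.

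**The concern.** The closing sentence of section 2.8 means that if the estimates agree, all of them are unbiased. That could be argued only if the biases really were unrelated. Under section 3.1, two of the three VE analyses draw on the same case series and the same register population, in the same territory and years. A factor tied to both vaccine uptake and diagnosed gonorrhoea enters both in the same way. Section 2.8 itself names one: healthcare seeking for STI treatment and for vaccination. Their agreement would then be reported as corroboration although it says nothing about such a factor.

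For IMD the screening and AIR pair is the whole VE triangulation. For gonorrhoea, a confounded secondary estimate could be presented as confirmed by a second method.

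**Working it through.** The sentence carries no figure, so there is nothing to reproduce. The check sets the two definitions side by side and then puts numbers in.

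**1. Same comparison.** With PCV the proportion of cases vaccinated and PPV the population coverage:

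- standard screening: VE = 1 − [PCV/(1−PCV)] / [PPV/(1−PPV)]
- AIR case–control: VE = 1 − odds(vaccinated | case) / odds(vaccinated | NT AIR, same age)

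PCV comes from the notified NT cases and PPV from the NT AIR. With the same vaccination definition and age- and time-specific coverage, these are one quantity. The comparison is not across contexts.

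**2. Worked example.** Coverage of 50% is from section 2.9.1. Assumed: a trait held by 40% of the population, vaccination OR 0.4, gonorrhoea risk ratio (RR) 4, true VE 0.

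- Coverage is 0.590 without the trait and 0.365 with it: 0.6×0.590 + 0.4×0.365 = 0.500.
- Vaccinated case weight: 0.6×0.590 + 0.4×4×0.365 = 0.938.
- Unvaccinated case weight: 0.6×0.410 + 0.4×4×0.635 = 1.262.
- PCV = 0.938/2.200 = 0.4265.
- VE = 1 − (0.4265/0.5735)/(0.5/0.5) = 0.256, by either method.

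**3. Simulation.** Population 14,077 (section 2.9; the figure is for ages 14–19), 1,350 cases (section 2.9.1), 20 age-matched AIR controls per case, conditional logistic likelihood, constant coverage, 25 runs per setting. The last column is the expected chlamydia-control VE if the trait raises chlamydia risk 4-fold or 2-fold.

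| True VE | Confounding (vaccination OR, gonorrhoea RR) | AIR | Screening | Chlamydia controls (RR 4 / RR 2) |
|---|---|---|---|---|
| 0 | none | −0.01 | 0.00 | 0.00 |
| 0 | 0.4, 4 | 0.26 | 0.26 | 0.00 / 0.13 |
| 0 | 2.5, 4 | −0.34 | −0.35 | 0.00 / −0.15 |
| 0.20 | none | 0.20 | 0.20 | 0.20 |
| 0.20 | 0.4, 4 | 0.40 | 0.40 | 0.20 / 0.31 |
| 0.20 | 2.5, 4 | −0.08 | −0.08 | 0.20 / 0.08 |

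The within-run difference between AIR and screening had an SD of about 0.01–0.02. The two agree as closely with the shared bias as without it.

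**4. Where they part.** In the confounded setting with true VE 0:

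- coverage building up over 18 months (assumed): AIR 0.21; screening 0.18 with time-averaged coverage, 0.59 with final coverage;
- uptake and risk both varying with age (assumed), coverage not split by age: AIR 0.26, screening 0.14;
- formula as printed, 1 − PCV(1−PCV)/[PPV(1−PPV)]: 1 − (0.4265×0.5735)/0.25 = 0.02, against 0.26 for AIR.

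The printed windows differ too. Screening takes gonorrhoea arising inside three months after two doses; case–control counts vaccination only if given at least three months before the case date.

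**5. A contrast that can fail.** In step 2, the vaccination odds ratio in chlamydia versus AIR controls is 0.74 if chlamydia shares the trait fully and 0.86 at RR 2. With at most 1,350×4 = 5,400 chlamydia and 1,350×20 = 27,000 AIR controls at 50% coverage, SE(log OR) = √[1/(5,400×0.25) + 1/(27,000×0.25)] = 0.030. Power would be about 40%, 94% and over 99% for an apparent VE against chlamydia of 5%, 10% and 15%. This counts all control slots as distinct people. They cannot be: about 14,077/6 × 8 = 18,769 people pass through ages 15–19 in three years (eight birth years, assumed equal in size).

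**The case against.** **Agreement is not guaranteed.** A reader might infer that the two analyses agree whatever the bias or effect, so that one estimate is reported twice. The documents do not support that. Coverage timing, age aggregation, and the formula and windows as printed all separate them (step 4). Nor do 27,000 control slots simply rebuild the register's coverage figure: the plan says up to 20 controls, matched on birth date, with vaccination status fixed at each case's date. The objection stands and limits the point to bias common to both analyses. It does not rescue the sentence, since divergence from a coverage or formula artefact says nothing about shared confounding.

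**The plan already holds an informative contrast.** Chlamydia controls are the primary analysis, use a different reference series and can disagree with AIR and screening. This stands, and the fix relies on it. Full agreement across all three is still not proof, because one case series feeds them all.

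**There is no formal decision rule.** Section 2.8 sets no threshold or action and speaks of only partial mitigation. The primary estimate and its test do not depend on the sentence. This stands: the fault lies in the stated inference.

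**Planned adjustment is ignored.** Section 2.8 will link subgroup background rates to individual records. That may shrink the bias, or separate the two estimates if it enters only one. Subgroup infection rates do not, however, measure individual healthcare seeking.

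**A negative-control check can mislead.** The article states no exclusion of chlamydia controls who also have gonorrhoea. With 10% or 30% co-infected (assumed), true VE 20%, 50% coverage and no bias, co-infected controls are 0.4/0.9 = 44.4% vaccinated. The expected OR is then 0.494/0.506 = 0.98 or 0.483/0.517 = 0.94. At SE 0.030 the interval excludes 1 in about 11% or 60% of studies. This stands, and rules out labelling or suppressing estimates automatically.

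**Conclusion.** The point holds in this limited form, and section 2.8 is wrong as written. The biases of screening and AIR case–control are not unrelated, screening as specified is not a cross-context comparison, and agreement does not imply that all analyses are unbiased. With definitions aligned, the two share confounding and ascertainment bias and differ by about 0.00–0.02 in VE whether that bias is nil, upward or downward. In one plausible setting both report 0.26 when the truth is 0.

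The 0.26 and −0.35 illustrate assumed confounder strengths and do not forecast this study's bias. The conclusion itself needs only the shared cases and reference population that section 3.1 specifies. It does not impugn the primary chlamydia-control estimate. It does change what the study may claim from concordant results, most of all for IMD.

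**What to change.** In section 2.8:

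1. Delete the closing sentence and the claims that the biases are unrelated and that screening is cross-context.
2. State that screening and AIR case–control are not independent evidence and that their agreement is not corroboration. Say this explicitly for IMD, where controls come only from the AIR.
3. For gonorrhoea, rest triangulation on the chlamydia-control versus AIR/screening contrast, and state beforehand the expected direction of each main bias in each analysis. Add that agreement of all three would not exclude bias in the common case series.
4. Report the odds ratio of vaccination in chlamydia versus AIR controls, with its confidence interval, as a negative-control check. Exclude chlamydia controls with concurrent gonorrhoea, allow for repeated sampling of the same people, and state the assumption that the vaccine has no effect on chlamydia. Interpret the result as evidence on bias, not as a trigger to label or withhold the AIR and screening estimates.

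The cost is a few sentences and one model on control sets that will be drawn anyway. The one loss is that fewer independent lines of evidence can be claimed.

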### 2.9. Sample Size

For ethical and equity reasons, all 14–19-year-olds in the NT in 2021–2022 will be eligible to be offered 4CMenB. The estimated eligible population is 14,077, of whom 5621 or 40% are Aboriginal or Torres Strait Islander (June 2016 estimates). We conservatively anticipate 40–50% participation of this population group and up to 30% non-return at 12 months due to factors such as interstate and intra-territory travel.

#### 2.9.1. Gonorrhoea Infection Power Calculations

Case–control study: To assess the vaccine effectiveness of 4CMenB on gonorrhoea, assuming 1350 cases of gonorrhoea among 15–19-year-olds in the NT (Australian Bureau of Statistics) over a three year period (i.e., 450 per annum), a ratio of 3 matched controls to 1 case and assuming 50% of the eligible control population vaccinated with a correlation of 0.1, the study has at least 90% power at alpha = 0.05 to detect vaccine effectiveness of at least 20% (i.e., OR = 0.8 or less) and allowing for correlation between cases and controls on basis of 0.2. With this estimated number of cases and controls, the study is adequately powered even if 40% of the eligible population is vaccinated.

Interrupted time series study: A power simulation study that assumed three years of monthly observations post-implementation in each of the vaccinated and unvaccinated groups, constant gonorrhoea counts over time in the unvaccinated group (i.e., ~450/12 = 37.5 cases per month, so µ = 3.62), and a Poisson distribution of counts was conducted. Using the method of Feiveson with 1000 runs, the power to detect a coefficient of −0.008 in the vaccinated group as significant is 0.84 (alpha = 0.05, two-tailed test). This equates to a 9.6% reduction in cases in the vaccinated group relative to unvaccinated group (from 450 to 407 cases p.a.), assuming the two groups are of equal size.

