## 4. Secondary Objectives

### 4.1. Gonorrhoea

Vaccine impact on gonorrhoea will be estimated using surveillance data from the CDC for laboratory-confirmed gonorrhoea cases, comparing six pre-vaccine surveillance years to three post-vaccination years. Interrupted time series analysis will be used to evaluate the impact through regression modelling. To estimate impact in each age group (15, 16, 17, 18, 19 years), incidence rate ratios will be estimated by comparing case numbers in the post-vaccination period with cases in the equivalent age cohort during the six pre-vaccination years. To take into account any changes over time unrelated to 4CMenB vaccination, the IRRs will be adjusted using the relevant annual gonorrhoea incidence in all adults who were not in the vaccine-eligible age cohorts.

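### The 84% power in section 2.9.1 is not the power of the interrupted time series in section 4.1, and it does not match the 9.6% reduction it is said to represent

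*Protocol article*

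**What the plan says.** The protocol article, section 2.9.1, describes a power simulation for the interrupted time series with these features:

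- **Data:** "three years of monthly observations post-implementation in each of the vaccinated and unvaccinated groups". No pre-vaccine months are mentioned.
- **Comparator:** "constant gonorrhoea counts over time in the unvaccinated group (i.e., ~450/12 = 37.5 cases per month".
- **Variation:** "a Poisson distribution of counts was conducted".
- **Result:** "the power to detect a coefficient of −0.008 in the vaccinated group as significant is 0.84". This rests on 1000 simulated data sets and a two-sided 5% level.
- **Interpretation:** "This equates to a 9.6% reduction in cases in the vaccinated group relative to unvaccinated group (from 450 to 407 cases p.a".), with the two groups taken to be equal in size.

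The preceding paragraph of section 2.9.1 uses 450 cases a year (1350 over three years) as the count for all NT 15–19-year-olds. Section 2.9 expects 40–50% participation.

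Section 4.1 describes the analysis itself as "comparing six pre-vaccine surveillance years to three post-vaccination years", with adjustment for incidence in adults outside the eligible cohorts. Table 1, objective 3, attaches the interrupted time series label to the same six-year/three-year comparison. It lists vaccinated against unvaccinated notifications as a separate outcome without that label.

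**The concern.** An interrupted time series needs a period before the interruption, and the simulation has none. It is a two-group comparison after implementation, which resembles the other outcome under Table 1's objective 3. The effect is stated once as a slope and once as a fixed percentage fall, and the two are not the same hypothesis. The unvaccinated group alone is given the case count of the whole age group.

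If the published impact result is null, readers will set it against 84% power for a fall of about 10%. That benchmark belongs neither to the planned model nor to the contrast described.

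**Working it through.** **Inputs from section 2.9.1.** 37.5 cases per month per group, 36 months, log-slope −0.008 in the vaccinated group, flat comparator, Poisson counts, two-sided alpha 0.05. I read the slope as per month, because the observations are monthly and 12 × 0.008 = 0.096 gives the stated 9.6%.

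**Formula.** For a log-linear Poisson model, the standard error (SE) of a coefficient is the root of its diagonal element in (XᵀWX)⁻¹, where W holds the expected counts. Power = Φ(|effect|/SE − 1.96). Simulation of the main variants agreed with this.

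**Step 1: reproduce 0.84.** Test the vaccinated series' own slope against zero:

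- 36 monthly points: SE 0.00281, ratio 0.008/0.00281 = 2.85, power 0.81.
- 37 points (t = 0 to 36): SE 0.00270, ratio 2.96, power 0.84.

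**Step 2: the contrast described, vaccinated against unvaccinated.**

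| Test, 37.5 per month in each group | SE | Power |
|---|---|---|
| Slope difference with group, time and group-by-time terms | 0.00384 (36 points); 0.00369 (37 points) | 0.55; 0.58 |
| Constant 9.6% reduction, 1350 against 1350 × 0.904 = 1220 cases | √(1/1350 + 1/1220) = 0.0395; log effect 0.101 | 0.72 |
| Time and group-by-time terms, common intercept forced | 0.0019–0.0020 | 0.98–0.99 |

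**Step 3: the conversion.** 450 × (1 − 0.096) = 407, so the stated reduction is 12 × 0.008 applied as a constant. Summing 37.5 × exp(−0.008t) over months 1–12, 13–24 and 25–36 gives 427, 388 and 353 cases. The total is 1168 against 1350, and 1 − 1168/1350 = 13.5%. At month 12 alone the rate is 1 − exp(−0.096) = 9.2% lower.

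**Step 4: the case count.** Two groups at 450 a year make 900 before any effect, against a stated total of 450. With 225 a year (18.75 per month) in each group, the slope difference has power 0.31–0.33 and the constant 9.6% reduction 0.44.

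**Step 5: the planned comparison.** One series at 37.5 per month, 72 pre and 36 post months, log-linear pre-trend. The two power columns test the slope change with and without a level-change term.

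| Scenario | With level term | Without level term |
|---|---|---|
| Slope change −0.008 in the whole age group, pure Poisson | 0.77 | 0.89 |
| Same, dispersion 1.5 (assumed) | 0.60 | 0.74 |
| Same, dispersion 2 (assumed) | 0.48 | 0.62 |
| About half vaccinated: population slope −0.004 (assumed), pure Poisson | 0.29 | 0.37 |

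A simple pre/post rate ratio without trend, for a constant 9.6% fall, has SE √(1/2700 + 1/1220) = 0.0345 and power 0.83 under pure Poisson variation.

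**The case against.** **Power of the planned analysis.** Section 4.1 does not say whether the model has a level term or a pre-trend. Under pure Poisson variation and the full effect, reasonable versions give 0.77, 0.83 or 0.89, which lie on both sides of 0.84. A reader might infer that the planned analysis has far less power than stated; the documents do not show this. The low figures need partial uptake or overdispersion. The first is what section 2.9 expects, but the slope of −0.004 is my approximation. For the second, section 2.8 lists changes in notification practice and case ascertainment as sources of bias, without giving a dispersion.

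**The figure of 0.55.** A reader might take this as the true power of the two-group comparison. It depends on fitting a group term, which the article does not specify. A forced common intercept gives 0.98–0.99. I think a group term is needed in practice, since the two groups will differ in size and baseline rate, but the text does not settle it.

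**The source of 0.84.** The own-slope test is an inference. With 36 points it gives 0.81, outside Monte Carlo error for 1000 runs (about 0.012 standard error), and the exact match needs 37 points. A common-intercept model at 225 cases a year per group also gives 0.81–0.84, but contradicts the stated 37.5 per month.

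**Relevance.** Table 1 does list a vaccinated-against-unvaccinated outcome, so part of the fault is the label. The calculation sets no sample size.

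All of this stands. None of it makes 0.84 the power of the six-year/three-year analysis, or −0.008 per month a fall from 450 to 407 a year.

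**Conclusion.** The point holds in this form. The 84% comes from a post-period-only, two-group Poisson calculation and is not the power of the analysis in section 4.1 and Table 1. The 9.6% conversion is an arithmetic error: the slope used implies a mean reduction of 13.5% over three years. At the stated counts, 0.84 fits only the vaccinated series' own slope, and the vaccinated-against-unvaccinated reading gives 0.55–0.58 or 0.72 unless a common intercept is forced. The 450 cases are counted twice.

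The direction of the error for the planned analysis is open under pure Poisson variation and full effect. It turns downward with the expected 40–50% uptake or with overdispersion; the sizes in those rows rest on assumed values. The paragraph should be corrected, but the objective is secondary and the primary case–control power is untouched.

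**What to change.** Rerun the simulation with the section 4.1 model: 72 pre and 36 post monthly counts, about 37.5 per month in total, the effect scaled to 40–50% coverage, and dispersion estimated from the six pre-vaccine years. State the fitted model, including whether it has a level term. Report the new power, and give the detectable effect as the mean reduction over the three post-vaccine years.

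If the vaccinated-against-unvaccinated calculation is kept, label it as power for that Table 1 outcome, state whether a group term is fitted, split the 450 cases between the groups and correct the 9.6% conversion.

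The cost is a few hours of simulation and one replaced paragraph. No participants or new data collection are needed. The stated power will change and, at the expected uptake, is likely to be lower.

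### The interrupted time series effect tied to power 0.84 is misdescribed: read as a monthly slope, −0.008 means about 13% fewer cases over three years, not 450 falling to 407 a year

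*Protocol article*

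**What the plan says.** The second paragraph of section 2.9.1 (Gonorrhoea Infection Power Calculations) describes a power simulation for the interrupted time series. It takes "three years of monthly observations post-implementation in each of the vaccinated and unvaccinated groups" and, for the comparison series, "constant gonorrhoea counts over time in the unvaccinated group (i.e., ~450/12 = 37.5 cases per month, so µ = 3.62"). Counts are Poisson. The result is reported as follows: "the power to detect a coefficient of −0.008 in the vaccinated group as significant is 0.84", at two-sided alpha 0.05 and from 1000 runs. The coefficient is then translated for the reader: "This equates to a 9.6% reduction in cases in the vaccinated group relative to unvaccinated group (from 450 to 407 cases p.a".), with the two groups taken to be of equal size.

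The text does not say whether −0.008 is per month, per year or a one-off shift. It also does not say that the 9.6% refers to a particular point in the three years.

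**The concern.** The last sentence presents the detectable effect as a plain difference in annual counts: 407 cases a year where there would have been 450. But 9.6% is exactly 12 × 0.008, which suggests a monthly slope multiplied up to one year, while the simulation runs for three. If so, the effect that earned the power of 0.84 keeps growing after month 12 and is larger than the one reported. A reader would then believe that the study can detect a smaller reduction than the one simulated.

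**Working it through.** **Inputs, all from section 2.9.1.** Mean 37.5 cases per month in the unvaccinated group (log mean 3.62), constant over time; 36 months after implementation; Poisson counts; coefficient −0.008; two-sided alpha 0.05; equal groups.

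**Step 1: where 9.6% and 407 come from.** 12 × 0.008 = 0.096, and 450 × (1 − 0.096) = 406.8. Both stated figures follow from multiplying the coefficient by 12.

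**Step 2: which reading gives the stated power.** The check is Wald power from the expected information of a Poisson log-linear model, with log mean 3.62.

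| Reading of −0.008 | Power |
|---|---|
| Slope per month in the vaccinated series, months 0 to 36 | 0.840 |
| Same, 36 points (1 to 36 or 0 to 35) | 0.81 |
| Level shift between groups | 0.055 |

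For the 36-point slope the standard error is about 0.00283, so z = 0.008/0.00283 = 2.83 and power is Φ(2.83 − 1.96) ≈ 0.81. For the level shift the standard error is 0.03865, so z = 0.008/0.03865 = 0.21. Monte Carlo error with 1000 runs is about 1.2 percentage points. The exact 0.84 therefore fits 37 time points better than 36, but only a monthly slope comes near it and also gives the 9.6%.

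**Step 3: what that slope implies.** The rate relative to the unvaccinated group at month t is exp(−0.008t).

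- Month 12: 1 − exp(−0.096) = 9.2%, an annualised rate of 450 × exp(−0.096) ≈ 409.
- Month 24: 1 − exp(−0.192) = 17.5%.
- Month 36: 1 − exp(−0.288) = 25.0%.

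Yearly cases are the sums of 37.5 × exp(−0.008t) over the months of each year:

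| | Year 1 | Year 2 | Year 3 | Three years | Reduction from 1350 |
|---|---|---|---|---|---|
| Months coded 1 to 36 | 427 | 388 | 353 | 1168 | 13.5% |
| Months coded 0 to 35 | 431 | 391 | 356 | 1178 | 12.8% |

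With the first coding the yearly reductions are 5.0%, 13.7% and 21.6%. No year has 407 cases under either coding. The annualised rate passes through 407 once, at t = ln(450/407)/0.008 = 0.1004/0.008 ≈ 12.6 months.

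**Step 4: the effect the sentence literally describes.** This step is an illustration only: three-year totals compared as two Poisson counts, with the plan's own numbers. A constant 9.6% reduction gives 1350 v 1350 × 0.904 ≈ 1220.

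- z = |ln 0.904| / √(1/1350 + 1/1220) = 0.1009/0.0395 ≈ 2.56, so power is Φ(2.56 − 1.96) ≈ 0.72.
- A constant 10.5% reduction gives 1350 v 1208: z = |ln 0.895| / √(1/1350 + 1/1208) = 0.1109/0.0396 ≈ 2.80, so power is about 0.80.

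**The case against.** The best defence is that 9.6% was meant as an annualised rate of decline. On that reading it is nearly right (the exact fall after one year is 9.2%, or 409 rather than 407), and the defect is a missing time unit. This stands as a likely account of how the sentence arose. It does not rescue the sentence, which gives a reduction in cases relative to the unvaccinated group, expressed as annual counts, and never says that the decline continues to 25%.

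It is also fair that the monthly unit is inferred, and that the 36 points described give 0.81 rather than 0.84. The inference is strong because no other reading fits both figures, but it remains an inference.

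Three stronger readings are tempting and not supported.

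- **That a slope was the wrong effect to simulate.** The documents do not show this. Vaccine is offered over 2021–2022 (section 2.9), the doses are at least two months apart (section 2.2), and a gradual build-up of effect is a defensible assumption.
- **That the planned analysis has only 0.72 power for a 9.6% reduction.** The 0.72 comes from a simple comparison of totals. Section 4.1 plans an interrupted time series with six pre-vaccine and three post-vaccine years, with adjustment for incidence in adults outside the eligible cohorts. Power for a level change under that model has not been computed.
- **That the case counts given to each group are too high, because 450 a year is also the figure for the whole Territory.** That is a separate question about the inputs. It would need an assumed split of cases, and the conversion fails without it.

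**Conclusion.** The stated equivalence does not follow from the plan's own inputs. If −0.008 is a slope per month, the effect associated with the power of 0.84 is a continuing decline of about 0.8% per month. Cases fall by about 13% over three years (12.8% to 13.5%, depending on how months are coded), and the rate is 25.0% lower at month 36. The 9.6% approximates one year of that slope. It is not a reduction in annual cases sustained over the period simulated.

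The error makes the detectable effect look smaller than it is. By the simple comparison of totals, the gap for a sustained reduction is modest: about 10.5% for 80% power, against the 9.6% stated with 0.84.

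The conclusion rests on the inferred monthly unit and on the plan's mean of 37.5 per month in the unvaccinated group. The interrupted time series serves a secondary objective (section 4.1 and Table 1), and the primary case–control and carriage calculations do not use this figure.

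**What to change.** State that the coefficient is per month, and replace the equivalence with the effect simulated: a decline of about 0.8% per month, about 13% fewer cases over three years, and a rate 25% lower by month 36. The number and coding of time points should be given too, so that the 0.84 can be reproduced.

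If a sustained reduction is the intended target, re-simulate a level change under the planned interrupted time series model and report the reduction detectable at the stated power.

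The first option costs one sentence and the second one re-run of the simulation. Neither changes recruitment or data collection. The price is a less favourable stated detectable effect.
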